### Exclusion Criteria

Participants will be excluded from the study if (1) they are younger than 16 years old, (2) they score below the cutoff point for severe suicidal thoughts (SIDAS score <21), (3) they score above the cutoff point for severe suicidal thoughts (SIDAS score ≥21) and report being likely to contact the suicide prevention helpline. They will be directly transferred to the contact details of the helpline.

People who do not meet the inclusion criteria will be directed to a web page thanking them for their time and encouraging them to contact the helpline if they feel distressed.

### Sample Size

When assuming probabilities of 0.49 and 0.39 for contacting the helpline for the intervention group and the control group, respectively (based on Jaroszweski et al [15]), a power of .8 and alpha of .05, a sample size calculation for logistical regression analysis (2-tailed) indicates a total sample size of 775 participants [21]. We estimate that about 10% of participants drop out during the intervention; therefore, at least 853 participants have to be included. Furthermore, we estimate that approximately 30% of respondents score below the cutoff point for high risk of suicidal behavior, and based on Jaroszewski et al [15], we expect that 20% of respondents will indicate a high probability of contacting the helpline [15]. We, therefore, estimate that a minimum of 1706 respondents need to be recruited. We will continue to recruit participants until there are enough participants per condition.

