**Methods:**

People visiting the self-test for suicidal thoughts on the website of the suicide prevention helpline will be asked to participate in a study to improve the self-test. Individuals with severe suicidal thoughts and little motivation to contact the helpline will be randomly allocated either to a brief BRI, in which they will receive a short tailored message based on their self-reported barrier to the helpline (n=388) or care as usual (general advisory text, n=388). The primary outcome measure is the use of a direct link to contact the helpline after receiving the intervention or control condition. Secondary outcomes are the self-reported likelihood of contacting the helpline (on a 5-point scale) and satisfaction with the self-test. In the BRI, participants receive tailored information to address underlying concerns and misconceptions of barriers to the helpline. A pilot study was conducted among current test-takers to identify these specific barriers.

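### The 10% drop-out allowance was added (853) when it should have been divided out (862), and the abstract's 776 randomised conflicts with the 853 to be included

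*Protocol article*

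**What the plan says.** The Sample Size section of the protocol article builds its target in three steps.

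- Base requirement: "When assuming probabilities of 0.49 and 0.39 for contacting the helpline for the intervention group and the control group, respectively", with "a power of .8 and alpha of .05", from which "a sample size calculation for logistical regression analysis (2-tailed) indicates a total sample size of 775 participants".
- Drop-out: "We estimate that about 10% of participants drop out during the intervention; therefore, at least 853 participants have to be included".
- Screening: about 30% of respondents are expected to fall below the SIDAS cutoff and 20% to report that they are likely to contact the helpline. The authors therefore "estimate that a minimum of 1706 respondents need to be recruited".

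The section closes by saying that recruitment goes on until each condition has a sufficient number of participants. It does not state that number.

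The Methods paragraph of the abstract describes random allocation to a tailored message based on the participant's "self-reported barrier to the helpline (n=388) or care as usual (general advisory text, n=388"). The Procedure section places randomisation directly after inclusion, before the barrier questionnaire and the advisory text. The Statistical Analysis section plans an intention-to-treat analysis with missing values imputed by MICE.

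**The concern.** There are two separate faults.

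First, the drop-out is stated as a share of participants, that is, of those who enter. An allowance for a loss of that kind is made by dividing by the retained fraction. Multiplying by 1.10 gives a total that, after the stated loss, falls below the requirement it was meant to protect.

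Second, the article gives two totals for what should be one quantity. Participants are randomised as soon as they are included, and the expected drop-out happens during the intervention. The number included and the number randomised should therefore be the same, yet the abstract gives 776 and the Sample Size section at least 853. The recruitment rule does not settle which governs, because it names no figure. The only per-condition figure in the article is the abstract's 388.

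At stake are a correct and consistent randomisation target, and a small amount of power.

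**Working it through.** **Inputs** (all from the Sample Size section unless noted): p1 = 0.49, p2 = 0.39, two-sided alpha 0.05, power 0.80, base total 775, drop-out 10%, included 853, recruited 1706, and 388 per arm (abstract, Methods).

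**1. Reproduce the base figure.** Pooled two-proportion formula, per arm:

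n = [1.960 × √(2 × 0.44 × 0.56) + 0.8416 × √(0.49 × 0.51 + 0.39 × 0.61)]² / 0.10²

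= [1.960 × 0.7020 + 0.8416 × 0.6984]² / 0.01 = 385.6, so 386 per arm and 772 in total.

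Two logistic-regression formulas give 771.2 (binary covariate) and 776.4 (Wald test, odds ratio 1.503). The stated 775 is reproduced and is not in question.

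**2. Reproduce 853.**

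- 775 × 1.10 = 852.5, rounded up to 853. This matches the article.
- 775 / 0.90 = 861.1, rounded up to 862.

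**3. Reproduce 1706.** The article adds the two screening losses: 30% + 20% = 50%.

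- 853 / 0.50 = 1706. This matches the article.
- 862 / 0.50 = 1724.

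**4. Apply the plan's 10% loss to each total.** With n completers per arm, power = Φ[(0.10 × √n − 1.960 × 0.7020) / 0.6984].

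| Randomised | Expected completers | Power among completers |
|---|---|---|
| 862 | 862 × 0.9 = 775.8 | 80.2% |
| 853 | 853 × 0.9 = 767.7 | 79.8% |
| 776 (only if the abstract is taken literally) | 776 × 0.9 = 698.4 | 76.0% |

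For reference, 775 completers give 80.2% on the same formula.

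**5. Compare the totals.**

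- 862 − 853 = 9 participants, or 9 / 853 = 1.1%.
- 388 + 388 = 776, which is 775 rounded up to an even number and so carries no drop-out allowance.
- 853 − 776 = 77, the gap between the two totals printed for inclusion and randomisation.

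**The case against.** **The arithmetic slip is almost without effect.** This stands. Nine participants is close to the spread between accepted formulas for the base figure (771 to 776), and power falls only 0.2 points below the stated 80%. The drop-out rate is also given as approximate: 853 leaves 775 if the loss is 78 / 853 = 9.1%. The stated minimum still does not follow from the stated 10%.

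**The totals are floors, and recruitment continues as needed.** This stands too. Both 853 and 1706 are given as minimums, and a rule tied to numbers per condition can absorb a drop-out above 10%. It protects power only once the sufficient number is defined and counted in completers.

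**The abstract may mean the number analysed.** This is plausible, since 388 per arm is the base requirement made even. On that reading the two sections fit together and 776 meets the requirement. The abstract's wording, however, is about allocation, so it needs correcting.

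**The analysis is intention-to-treat with imputation.** The power figures above are for completers, not for the planned analysis. Imputing a missing outcome does not generally restore the information in an observed one, and the plan itself treats drop-outs as lost by inflating for them. This softens the consequence but does not justify 853.

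**A stronger reading that a reader might infer:** that the trial is set to run at 76% power. The documents do not support it. It requires recruitment to stop at 388 randomised per arm, and the Sample Size section calls for at least 853 included.

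**Conclusion.** The point holds in two limited parts. The allowance was computed as 775 × 1.10 when the stated loss calls for 775 / 0.9. The minimum should therefore be 862 included and 1724 recruited, in place of 853 and 1706. The effect is small: about 768 expected completers against 775, and 79.8% power among completers against the stated 80%.

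The conflict between 776 randomised (abstract) and at least 853 included (Sample Size, with randomisation straight after inclusion under Procedure) is the more useful one to resolve, because it leaves the randomisation target unclear. The 76.0% figure is conditional on misreading 776 as the randomised total and is not a forecast.

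These results rest on the plan's own 0.49 and 0.39, exactly 10% loss, the plan's 50% screening yield, the pooled two-proportion formula, and power counted in completers.

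**What to change.** 1. In Sample Size, change 853 to 862 (431 per arm) and 1706 to 1724. Alternatively, keep 853 and 1706 and state that about 768 completers and 79.8% power are expected.
2. In the abstract, give 388 per arm as the number completing or analysed, and about 431 per arm as the number randomised. If 853 is kept, the randomised figure is about 427 per arm (853 / 2 = 426.5).
3. Keep the rule that recruitment continues, but define the sufficient number as 388 participants per condition who complete the intervention or control condition. Treat 862 as a planning figure and not as a hard stop. A fixed stop would give no protection against a higher loss: at 15% drop-out, 862 × 0.85 = 733 completers. The rule also covers rounding, since 431 × 0.9 = 387.9 per arm.

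The cost is a few corrected figures and one defined phrase. The larger target means 9 more randomised and 1724 − 1706 = 18 more recruited, which is trivial against the roughly 4000 self-tests a month reported in the Introduction.

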### Procedure

After giving their informed consent and stating that they are 16 years or older, participants will be transferred from the helpline’s website to the Qualtrics platform. Figure 1 displays the study’s flowchart. During the screening phase, respondents start with the self-test. The self-test includes the SIDAS, which consists of 5 items on a 10-point scale measuring the frequency of suicidal thoughts, controllability, closeness to an attempt, distress, and interference with daily activities [17]. The self-test also contains questions regarding gender, age, and if the test-taker is currently in treatment for mental health problems. As mentioned in the exclusion criteria, if respondents score below the cutoff point for severe suicidal thoughts or score above the cutoff point but report that they are likely to contact the helpline, they will be excluded from the RCT.

After inclusion, participants will be randomly assigned to either the intervention or control condition. In both conditions, participants receive a barrier questionnaire to identify the reason why their self-reported likelihood of contacting the helpline in the screening phase was not very likely. After the barrier questionnaire, they receive a general advisory text (control) or an advisory text based on their selected barrier.

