### Statistical Analysis

The analyses will be carried out with an intention-to-treat analysis. Missing values will be imputed using the MICE package in R (v4.2.2; R Core Team 2022) [25]. In order to verify the randomization process and inspect drop-outs, independent *t* tests and chi-square tests will be used to determine whether the control group and the intervention group, as well as the completers and noncompleters, are comparable on baseline factors (ie, gender, age, SIDAS score, and in treatment or not). Chi-square analysis will also be used to test the hypothesis that participants who receive the brief BRI are more motivated to contact the suicide prevention helpline (using the direct link yes/no) than participants in the control condition. To evaluate the effectivity of the BRI in increasing service use by men and middle-aged people, and to examine potential moderators, logistic regression analysis will be used.

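### Randomising after the shared barrier questionnaire, instead of before it, would spare some avoidable post-randomisation losses at little cost (optional improvement)

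*Protocol article*

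**What the plan says.** The Procedure section of the protocol article fixes the order of steps. Allocation follows eligibility directly, and the next step is common to both arms: "After inclusion, participants will be randomly assigned to either the intervention or control condition. In both conditions, participants receive a barrier questionnaire". Only then do the arms part: "After the barrier questionnaire, they receive a general advisory text (control) or an advisory text based on their selected barrier".

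Three other statements bear on this:
- Sample Size allows for attrition without saying where in the flow it happens: "We estimate that about 10% of participants drop out during the intervention".
- Statistical Analysis states: "The analyses will be carried out with an intention-to-treat analysis". It adds that missing values will be imputed with the MICE package.
- Measures defines the primary outcome as use of the direct link once the assigned condition has been completed.

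The article gives no reason for allocating before the questionnaire. The flowchart (Figure 1) is not reproduced in the text at hand, so the order rests on Procedure alone.

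**The concern.** Randomisation sits one step earlier than the contrast needs. A person who closes the browser at the barrier questionnaire counts as randomised but has met nothing that differs between the arms. Intention to treat keeps that person in the analysis, and there are two ways to handle the missing outcome:

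- **Count as non-use.** Link use in both arms is multiplied by the same factor below 1, so the absolute difference shrinks.
- **Impute.** Part of the primary result then rests on modelled link use for people who saw neither text. These values add no information on the effect of the texts.

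The data are anonymous and there is no follow-up, so these outcomes cannot be recovered later.

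A lesser point is that the selected barrier determines which tailored text is shown and is a natural candidate for the planned moderator analysis. In the present order it is formally recorded after allocation and cannot be used to stratify it.

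**Working it through.** **Inputs from the Sample Size section**
- Rates: "When assuming probabilities of 0.49 and 0.39 for contacting the helpline for the intervention group and the control group".
- Error rates: "a power of .8 and alpha of .05", two-tailed.
- Stated total 775, raised to 853 for 10% dropout (775 × 1.10 = 852.5). I take 853 as the number entering the questionnaire.

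**Assumption.** The share d who leave at the questionnaire is not stated. I use 2%, 5% and 10% of entrants, equal in both arms, within a total loss of 10%. Any remainder leaves after the text.

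**Step 1: reproduce the plan's figure.** The pooled two-proportion formula is

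n per arm = [1.96 × √(2 p̄(1 − p̄)) + 0.842 × √(p1(1 − p1) + p2(1 − p2))]² / (p1 − p2)²

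With p1 = 0.49, p2 = 0.39 and p̄ = 0.44 it gives 386 per arm, 772 in total. The Wald formula on the log odds ratio gives 776. The stated 775 is reproduced.

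**Step 2: power formula**

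power = Φ[(p1 − p2 − 1.96 × se0) / se1], with se0 = √(2 p̄(1 − p̄)/n) and se1 = √([p1(1 − p1) + p2(1 − p2)]/n)

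**Step 3: randomise before the questionnaire, all leavers counted as non-use.** The 10% total loss gives 0.49 × 0.90 = 0.441 and 0.39 × 0.90 = 0.351, a difference of 9.0 points. With 853/2 = 426.5 per arm, power is 76.7%. This does not depend on where in the flow the 10% leave.

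**Step 4: randomise after the questionnaire, same 853 entrants.** The number randomised is 853 × (1 − d). Rates among them are multiplied by 0.90/(1 − d), because later leavers still count as non-use.

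| Leave at questionnaire (d) | Randomised | Rates | Difference | Power if before | Power if after | Gain |
|---|---|---|---|---|---|---|
| 2% | 836 | 0.450 vs 0.358 | 9.2 points | 76.7% | 77.3% | 0.6 points |
| 5% | 810 | 0.464 vs 0.369 | 9.5 points | 76.7% | 78.2% | 1.4 points |
| 10% | 768 | 0.490 vs 0.390 | 10.0 points | 76.7% | 79.8% | 3.1 points |

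(Gains are taken from unrounded power.)

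**Step 5: the planned imputation instead.** If MICE includes arm in the model and data are missing at random, the difference is not shrunk. Power is about that of the completers in either order: 853 × 0.90 = 768, 0.49 vs 0.39, 79.8%. The power gain is then about zero. What changes is the number of primary outcomes to impute. Randomising before leaves 853 × 0.10 = 85. Randomising after leaves 853 × (0.10 − d), which is 68, 43 and 0 for d = 2%, 5% and 10%.

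**The case against.** The strongest reply is that the plan produces little or none of this loss in power. It names imputation, not non-use, as the treatment of missing values, and Step 5 shows that the power gain is then about zero. That stands. What remains is reliance on imputed outcomes for people who saw neither text.

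Second, nothing in the article places any dropout at the questionnaire. The list is deliberately short (six options, under Assessment of Barrier), and the whole task is meant to take at most 10 minutes. That also stands, and it is why the result is a range. If most people leave after the text, most of the dilution is out of reach of this change.

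Third, the plan already raises the target to 853 and continues recruiting until each condition has enough participants. At the 388 per arm given in the abstract, power at 0.49 vs 0.39 is 80.2%. So a reader should not infer that the trial is underpowered because of this ordering.

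Fourth, a reader might infer bias between the arms, or a selected barrier distorted by allocation. The article supports neither. As Procedure describes it, both arms see identical screens until the advisory text, so neither leaving nor the barrier chosen should depend on arm. The barrier can already be used for adjustment or moderation; only stratified allocation is lost. An analysis set of those who reached the text would also be unbiased, and such a definition may stand in an analysis plan that is not shown.

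Finally, Assessment of Barrier describes the survey as part of the intervention, so keeping leavers could be defended as estimating the effect of offering the whole package. This carries limited weight, because Procedure gives the same questionnaire to the control arm and it cannot be part of the contrast.

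**Conclusion.** The point holds as a modest gain in precision and interpretability. Randomisation precedes a step common to both arms, and those who leave there are avoidable post-randomisation losses. With 853 entrants, 10% total loss and leavers counted as non-use, moving it is worth 0.6 to 3.1 power points as the share leaving at the questionnaire runs from 2% to 10%. The top of that range needs every dropout to fall at the questionnaire. Under imputation with data missing at random the power gain is about zero, and the benefit is up to 85 fewer imputed primary outcomes. All of this assumes loss unrelated to arm. It is a low-cost optional improvement; the validity of the comparison is not in question.

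**What to change.** In the survey flow, move the randomiser to the point immediately after the barrier item is submitted and before the advisory text. Change the matching sentence in Procedure, and define the intention-to-treat population as everyone randomised at that point. The selected barrier then becomes a true baseline variable; stratifying on it is optional. Report separately how many eligible people leave at the questionnaire.

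The cost is one change to the survey flow, best made before launch, with no new data items. There are two limits. The analysed population becomes those who complete the questionnaire, and dropout after the text remains and still has to be handled.

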**Figure 1 figure1:**
[figure not shown]
Flowchart. BRI: barrier reduction intervention; RCT: randomized controlled trial; SIDAS: Suicidal Ideation Attributes Scale.

### Measures

The primary outcome measure is the use of a direct link to the helpline after completing the intervention or the control condition. Due to the anonymous nature of the helpline, it is not possible to measure if people who do not directly use the link to the helpline, contact the helpline at a later point in time. Therefore, the self-reported likelihood of contacting the helpline will be included as a proxy measurement. This will be measured by the question “How likely are you to contact 113's helpline via chat or phone?” with answering options ranging from “not likely” to “very likely” on a 5-point scale. Other measures include gender, age group, SIDAS score, being in treatment for mental health problems (yes, no, and on a waiting list), and satisfaction with the self-test (Dutch CSQ-3) [22].

### Persuasive System Design Model

Preceding research and literature on the design of persuasive eHealth technologies often cover software or applications intended for continuous use, whereas our study entails a single-session intervention. With this in mind, the BRI has been designed with the use of the persuasive system design (PSD) model [23,24]. The PSD model is a framework for the development and evaluation of persuasive behavior change technologies and offers 28 design principles [23]. Table 1 gives an overview of the applicable and relevant principles for our intervention, the corresponding requirements, and the implementation goals for the BRI.

**Table 1 table1:** Design principles originating from the persuasive system design model applied to the intervention.

Principle [24]			Requirement		Implementation goals
**Primary task support**					
	Reduction (“A system that reduces complex behavior into simple tasks”)	The system should lower the barrier toward help-seeking; breaking it down into small steps.		Guiding toward the first small step in the help-seeking process: emphasis on different low-threshold methods of contact (24/7 chat and telephone) and the anonymous nature of the helpline	
	Tunneling (“Using the system to guide users through a process or experience provides opportunities to persuade along the way”)	The system should guide users in the attitude change process by providing means for action.		Self-test offers the test-taker information about the severity of their suicidal thoughts.	
	Tailoring (“Information provided by the system will be more persuasive if it is tailored to the potential needs, interests, personality, usage context, or other factors relevant to a user group”)	The system should provide tailored information based on the user’s level of suicidality and barriers toward the helpline.		User receives feedback on their level of suicidality. BRI^a^ provides different information based on the selected barrier.	
	Simulation (“Systems that provide simulations can persuade by enabling users to observe immediately the link between cause and effect”)	The system should persuade users to contact the helpline with experiences from others.		BRI provides statements of people with lived experiences of suicidality.	
**Dialogue support**					
	Similarity (“People are more readily persuaded through systems that remind them of themselves in some meaningful way”)	The system should be designed in such a way that users can identify with the stories.		BRI includes photos from people with lived experience and counselors of the helpline of different ages and gender.	
	Liking (“A system that is visually attractive for its users is likely more persuasive”)	The system should appeal to the target group.		Self-test and BRI use the same design and tone of voice as the helpline’s website.	
